### Secondary outcome measures

Secondary outcome measures will be documented at baseline and 16 weeks and will include:

(i) the function domain of the FHSQ [3];

(ii) the functional limitation, pain intensity and concern about appearance subscales of the MFPDI [49];

(iii) the number of DVA podiatry treatments required during the study period;

(iv) general health-related quality of life, assessed with the Short Form 12® Version 2.0 [69];

(v) the number of falls experienced during the follow-up period;

(vi) functional mobility, using the Timed Up and Go test [70];

(vii) presence of hyperkeratotic lesions (corns and calluses);

(viii) number of participants using co-interventions to relieve foot pain (such as oral non-steroidal antiinflammatory medications, topical medications and visits to other health-care practitioners), documented using a diary at 4, 8, 12 and 16 weeks, and;

(ix) participants’ perception of overall treatment effect at week 16, assessed with the question ‘Overall, how has your foot pain changed since the start of the study?’ with a five-point Likert scale response (‘marked worsening’, ‘moderate worsening’, ‘same’, ‘moderate improvement’, or ‘marked improvement’). For the purpose of analysis, this scale will then be dichotomized, where ‘success’ is defined as marked or moderate improvement on this scale.

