### Statistical analysis

Statistical analysis will be undertaken using SPSS version 20.0 (IBM Corp, NY, USA). All analyses will be conducted on an intention-to-treat principle using all randomized participants. Multiple imputation will be used to replace any missing data using five iterations, with age, baseline scores, and group allocation as predictors [72]. Demographic characteristics and baseline data will be summarized by descriptive statistics. Continuous data will be explored for normality using standard tests to satisfy the assumptions of parametric statistics. If data are found to be not normally distributed, transformation will be attempted using conventional techniques [73]. However, if data are still not normally distributed after transformation, non-parametric statistical tests will be used. Continuously-scored primary and secondary outcome measures with a normal distribution will be compared between groups using a linear regression technique with baseline scores, adjusted for by the analysis of covariance model [74,75]. Nominal and ordinal scaled data will be compared using chi-square analyses (or Fisher's exact test where appropriate) and Mann–Whitney *U*-tests, respectively. Effect sizes will be determined using Cohen’s *d*[76] for continuous data and relative risks for nominal data. Statistical significance for hypothesis tests will be set at the conventional level of α = 0.05.

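### Multiply imputed nominal and ordinal outcomes are assigned tests whose usual output Rubin's rules do not pool directly; run unpooled, they exceed the 5% level by about two to three points at 10% missing

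*Protocol article*

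**What the plan says.** All of the relevant rules but one stand in the Statistical analysis section of the protocol article.

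- Analysis set: "All analyses will be conducted on an intention-to-treat principle using all randomized participants".
- Missing data: "Multiple imputation will be used to replace any missing data using five iterations, with age, baseline scores, and group allocation as predictors".
- Tests: "Nominal and ordinal scaled data will be compared using chi-square analyses", with Fisher's exact test as the alternative and Mann-Whitney for ordinal data.
- Effect measure: "relative risks for nominal data".
- Continuous outcomes that fail normality: "if data are still not normally distributed after transformation, non-parametric statistical tests will be used".

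The nominal outcomes, listed under Secondary outcome measures, are presence of corns and calluses, use of co-interventions, and perceived treatment effect. The last is recorded on five ordered categories but analysed as yes or no: "this scale will then be dichotomized, where ‘success’ is defined as marked or moderate improvement on this scale".

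**The concern.** After multiple imputation, the standard analysis fits the same model to each completed data set and pools the estimates. The pooled variance adds the spread between data sets to the average variance within them, and that added term carries the uncertainty due to missing values. The ANCOVA chosen for continuous outcomes fits this directly, because it yields a coefficient and a standard error. Chi-square, Fisher and Mann-Whitney tests, as usually reported, do not.

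Followed literally, the plan therefore produces one p-value per completed data set for each nominal outcome. Each is computed as if all 120 outcomes had been seen. Two things are at stake. Each such p-value is too small on average, so the stated 0.05 level is exceeded. The p-values can also fall on both sides of 0.05, with nothing in the text to say which one counts. Testing complete cases instead would avoid both problems but would break the rule that everyone randomised is analysed.

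**Working it through.** **Inputs from the protocol article.** 60 per group, 10% drop-out, difference 12.5 and SD 23 (Sample size); α = 0.05, taken as two-sided (Statistical analysis). The five iterations are read as m = 5 imputed data sets; the wording is ambiguous.

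**The plan's own figure.** n = 2 × (1.96 + 0.84)² × 23² / 12.5² = 2 × 7.849 × 529 / 156.25 = 53.1, so 54 per group; 54 / 0.9 = 60. The stated size reproduces and is not in dispute. Ten per cent missing means 6 of 60 per arm.

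**Closed-form check, one completed data set.** Let a fraction f be missing completely at random, with imputation within arm from a drawn event rate. The variance of an arm's completed-data proportion, in units of p(1 − p), is 1/n_obs + f²/n_obs + f/n. The chi-square test assumes 1/n.

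- f = 0.10: 1/54 + 0.01/54 + 0.1/60 = 0.02037, against 1/60 = 0.01667. Ratio 1.222, square root 1.106. Type I error = 2 × [1 − Φ(1.96/1.106)] = 7.6%.
- f = 0.05: ratio 1.105, type I error 6.2%.
- f = 0.20: ratio 1.500, type I error 11.0%.

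The event rate cancels, so to this approximation the inflation does not depend on it.

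**Simulation.** 60 per arm, five imputations within arm, missing completely at random. The binary case assumes a 40% event rate in both arms (20,000 trials per setting). The ordinal case assumes a five-level scale (5,000 trials per setting). Only the 10% missing figure comes from the document.

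Pooling formulas:
- Log relative risk q = ln(a/b) for event counts a and b, with variance u = 1/a − 1/60 + 1/b − 1/60. Rubin: T = mean(u) + (1 + 1/5) × B, where B is the between-set variance of q.
- D2 for chi-square X on 1 df: r = 1.2 × var(√X); D2 = [mean(X) − (6/4) r] / (1 + r), referred to F with 1 and 4(1 + 1/r)² df.
- Mann-Whitney: W/3600 − 0.5, W being the U statistic for the intervention arm, with its tie-corrected rank variance, pooled by Rubin's rules.

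| Type I error | 5% missing | 10% missing | 20% missing |
|---|---|---|---|
| Chi-square, one data set | 6.4% | 7.7% | 10.9% |
| Chi-square, median of five p | 6.0% | 6.7% | 9.2% |
| Chi-square, smallest of five p | 10.0% | 14.0% | 23.3% |
| Chi-square pooled by D2 | 5.0% | 4.7% | 5.0% |
| Pooled log relative risk | 4.5% | 4.3% | 4.4% |
| Chi-square, complete cases | 4.9% | 4.7% | 5.2% |
| Mann-Whitney, one data set | 6.6% | 7.2% | 10.5% |
| Mann-Whitney, median of five p | 6.3% | 6.1% | 8.9% |
| Mann-Whitney pooled | 5.6% | 4.6% | 5.0% |

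Simulation error near 5% is about √(0.05 × 0.95 / 20,000) = 0.15 points for the binary rows and √(0.05 × 0.95 / 5,000) = 0.31 points for the ordinal rows.

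**Conflicting p-values at 10% missing.** The five chi-square p-values straddle 0.05 in 11% of null trials and in 26% of trials with assumed rates of 30% and 50%. For Mann-Whitney the figures are 10% under the null and 29% with an assumed latent shift of 0.45 SD.

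**The case against.** The strongest reply is that the gap is only an unstated combining rule, and a journal article may leave that to a fuller document. Much of this stands. The article never says results will stay unpooled, and it gives no combining rule for continuous outcomes either. What remains is that for ANCOVA the standard rule applies without further thought, whereas here the article itself has fixed tests to which that rule does not directly apply.

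A reader might infer that these tests cannot be pooled at all. That is too strong. D2 combines chi-square statistics, and Mann-Whitney pools through its probability estimate and rank variance; both hold the level in the table. Fisher's exact test is the hard case. A reader might also infer a 14% error rate, but that requires picking the smallest p-value, and nothing in the plan suggests this.

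The planned relative risk is a poolable quantity, but the article names it as an effect size and leaves the hypothesis test to chi-square or Fisher. A pooled relative risk could then sit beside an unpooled p-value that disagrees with it.

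Three further points limit the size. The Sample size section reports under 5% drop-out over 12 months in an earlier trial by the same team, where the inflation is only about one point. The simulation omits age and baseline scores from the imputation; where they predict the outcome, the spread between data sets would be smaller. And the only outcome recorded on a single ordered scale is dichotomised, so the ordinal half applies mainly if a continuous outcome fails normality.

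**Conclusion.** The concern holds in a limited form. The plan pairs multiple imputation with tests whose usual output does not pool directly. Used without a special combining rule, they give about 7% to 8% type I error from one completed data set at 10% missing, and about 6% to 7% from the median p-value. At 5% missing both are about 6%. Pooled tests stay at about 4% to 5% at 10% missing.

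These sizes rest on data missing completely at random, imputation within arm, five imputed data sets, and the assumed 40% event rate or five-level scale. They describe what happens if results are left unpooled; the document does not say that they will be.

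The nominal outcomes affected are secondary. The primary outcome is planned for ANCOVA, which pools directly, and meets this problem only if the non-normality fallback is triggered. The documents do not support reading this as a fault in the primary analysis as planned. The change is worth making but is not critical.

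**What to change.** Change the sentence on nominal and ordinal tests as follows.

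- **Nominal outcomes:** in each imputed data set, estimate the relative risk already planned, for example by modified Poisson regression (log link, robust standard error) on randomised group. Pool the log relative risk by Rubin's rules and take both the p-value and the 95% CI from the pooled estimate.
- **Sparse arms:** where an arm has no or very few events, the log relative risk is undefined or unstable. Use a pooled risk difference, or the chi-square combined by D2.
- **Any outcome sent to the Mann-Whitney route:** pool the Mann-Whitney probability with its rank variance, or a proportional-odds estimate.
- **Chi-square, Fisher and Mann-Whitney:** keep them as labelled complete-case checks.

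The cost is a few sentences and slightly more analysis work, with no new data. P-values will be somewhat larger. With assumed rates of 30% and 50% and 10% missing, the rejection rate is 53.8% for the pooled log relative risk and 55.3% for D2. One completed data set rejects in 61.3% of trials, but that test does not hold its level. Under the simulated mechanism the complete-case chi-square rejects in 56.9%, so pooling is chosen here to keep everyone randomised in the analysis, not to gain power.

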## Discussion

Footwear plays an important role in the maintenance of foot health and mobility in older people, and it has long been recognized that suboptimal footwear can be detrimental [77,78]. The provision of appropriate footwear, therefore, has considerable potential to reduce pain and improve health-related quality of life in this age-group. Although several studies have been undertaken to assess the effectiveness of footwear interventions in reducing foot pain in people with rheumatoid arthritis and other degenerative foot disorders [79-81], none have focused on the general veteran community. The study outlined in this protocol is, therefore, novel in that it targets a specific group of veterans (those ineligible for medical grade footwear) and uses generic, off-the-shelf footwear as the intervention.

Participants will be followed up at four-weekly intervals up to 16 weeks. This is longer than previous footwear intervention studies, which have employed 8 week [79] or 12 week [80,81] follow-up periods. We are, therefore, confident that the duration of the study is sufficient to detect differences between the groups, if they exist. Furthermore, previous footwear studies have been limited to single baseline and follow-up assessments [79-81], whereas our study will incorporate five repeated measurements for the primary outcome measure (baseline, 4 weeks, 8 weeks, 12 weeks and 16 weeks). This will provide additional insight into the trajectory of any improvements in participants’ foot pain. However, to address the issue of multiple testing of serial measurements [82,83], we have pre-specified 16 weeks as the primary end-point, and no statistical comparisons of the 4, 8 and 12 week scores will be undertaken.

Poor adherence is a well-recognized problem with footwear intervention studies [71,80,84] and has been attributed to the unique role of footwear as both an item of clothing and a health-related intervention [85]. We expect that the level of adherence to the off-the-shelf footwear in this study will be higher than that associated with medical grade footwear, due to better cosmesis. Furthermore, the initial postal invitation to take part in the study will specify the type of footwear that will be provided (accompanied by photographs), thereby providing veterans with an opportunity to decline participation on the basis of dissatisfaction with the appearance of the footwear. However, it is still likely that some participants will not be satisfied with the footwear either at the point of issue or during the follow-up period. The inclusion of baseline questionnaires addressing participants’ immediate perceptions of the attractiveness, comfort and usability of the footwear may provide useful insights into their adherence during the trial.

There are three key limitations of the study design that warrant careful consideration. Firstly, due to the nature of the intervention, it will not be possible to blind participants to their group allocation, nor will it be possible to blind the investigators providing the intervention. Secondly, because the ‘usual care’ control group will receive no additional treatment until the completion of the study, there is a risk of what is often referred to as ‘resentful demoralization’. That is, participants allocated to the control group may be resentful of not receiving the intervention, which may affect their adherence to the tasks required of them in the study and systematically influence their responses to the outcome measure questionnaires [86]. While this cannot be completely avoided, it may be offset to some extent by the fact that the control group participants will receive the intervention footwear at the completion of the trial, free of charge - footwear that they would not otherwise be eligible for under the DVA program. One suggested approach to address this issue is to document participant group allocation preference as a prognostic variable and consider this in the statistical analysis [87]. However, this would not be appropriate in our study, as it is unlikely that any participants would prefer to wait 16 weeks for their footwear rather than receiving it at the commencement of the study. Finally, this trial has been pragmatically designed to ensure that the findings can be easily translated into ‘real world’ situations, where off-the-shelf footwear is most often purchased without clinical assessment or diagnosis from foot health professionals. As such, we have not restricted the inclusion criteria in relation to the underlying *cause* of foot pain, so it is possible that our sample will include some participants with conditions that may not be amenable to treatment with footwear.

## Trial status

In summary, this study will be the first randomized controlled trial investigating the effectiveness of off-the-shelf footwear in reducing foot pain in Australian DVA clients ineligible for medical grade footwear. The study findings will be used to make evidence-based recommendations regarding the potential role of this intervention and will help inform the footwear provision component of the Rehabilitation Appliances Program of the DVA. Recruitment of participants commenced in October 2012 and final results are expected to be available in November 2013.

## Abbreviations

DVA: Department of Veterans’ Affairs; FHSQ: Foot Health Status Questionnaire; MFPDI: Manchester Foot Pain and Disability Index.
